#### **2.4.4.5 Blinding**

The teams are organized in such a way that coaches are the ones planning all the activities to be performed by the players. In this study they are the ones responsible for implementing the intervention programme. Therefore, it is not possible to blind the coaches or the players to the allocation of the teams in either the intervention or the control group. The researcher will not be blinded to team allocation but the research assistants will be blinded to team allocation as each assistant will be assigned to one team without any information about whether the team is in the intervention or control group. Research assistants will not know the type of intervention provided to the coaches.

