### **2.3.5.4 Injury registration form**

Similar to the exposure form, an injury report form (Appendix D) will be used to collect data pertaining to the incidence of injuries by the team medical personnel or the research assistant for

the teams that do not have any medical personnel (Fuller et al., 2006). The form is comprehensive and designed in such a way that the injuries are recorded on the front side of the page while all the definitions pertaining to the type, anatomical location, severity and circumstance of injury are provided at the back page of the form. The form has been developed and used during major FIFA tournaments and Olympic games (Junge, 2004) and has been extensively used in other studies (Junge et al., 2011) but is not routinely used in soccer in Rwanda. For example an injury is defined as any physical complaint that resulted from soccer participation whether in training or match. It does not necessarily mean that there is a need or not of medical attention.

A meeting with the team medical personnel will be organized to explain to them about the purpose of the study and their role in the study. They will be given the report forms to record any injury that will happen during the time of the study. Further explanations will be given to them as to specific definitions and the way of recording.

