#### **2.4.7.2 Compliance**

Compliance with the programme will be assessed by providing to the coaches with additional forms to record the details of each time the “11+” will be used as the warm up into the team as well as the number of players who performed them (Appendix N). Completeness of the forms will be reviewed regularly by the research team.

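### Research assistants are declared blinded, but the plan's procedures do not protect that blinding, and the injury outcome leaves room for the recorder's judgement

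*Combined protocol and SAP*

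**What the plan says.** Section 2.4.4.5 accepts that "it is not possible to blind the coaches or the players to the allocation of the teams" and that the researcher is also unblinded. It then states that "the research assistants will be blinded to team allocation as each assistant will be assigned to one team without any information" about which arm the team is in, and adds: "Research assistants will not know the type of intervention provided to the coaches".

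Three other sections bear on this claim:

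- **Who records injuries.** Section 2.3.5.4 provides a form to "collect data pertaining to the incidence of injuries by the team medical personnel or the research assistant for" teams that lack such staff. Section 2.4.7.1 carries season-one data collection into season two, the trial season.
- **What counts as an injury.** In section 2.3.5.4, "an injury is defined as any physical complaint that resulted from soccer participation whether in training or match". Whether medical attention is needed does not decide the matter.
- **Who sees the 11+ forms.** Under section 2.4.7.2, coaches log each use of the programme on the Appendix N form. The section ends: "Completeness of the forms will be reviewed regularly by the research team".

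**The concern.** Coaches, players and the researcher are openly unblinded, so any claim of blinded injury recording rests on the research assistants. The only safeguard given is that each assistant has one team and is not told its arm. A form showing that a team performs the 11+ reveals the arm at once.

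The outcome makes this matter. A wide injury definition takes in minor complaints, and whether these are written down depends on the recorder. If recording habits differ by arm, the injury rates can differ without any prevention effect, or a real effect can be hidden. A trial report that followed section 2.4.4.5 would also claim a safeguard that the conduct of the study may not have provided.

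**Working it through.** The plan gives no figure on this point, so the check sets its sections side by side.

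**1. Does the term research team include the assistants?** Section 2.3.5.3 has the fortnightly exposure forms collected by the research team. Section 2.3.6.1 describes the same collection as done by the researcher or the research assistants. Section 2.3.5.5 has research team members monitor the test circuits and, in the same paragraph, speaks of training the assistants in the measurements. By the plan's own usage the term includes them. That they review the 11+ forms under section 2.4.7.2 is therefore an inference, but no section excludes them.

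**2. Are there other routes to the allocation?** Section 2.4.7.1 lets assistants collect coach questionnaires in the preseason. Section 2.4.5.1 says these ask about first aid or injury prevention training. A questionnaire completed before training reveals nothing about the arm; one completed after it can. Section 2.4.7.1 does not say who collects the post-training round, so this route is also partly inferred. In addition, coaches and players know their arm (2.4.4.5, 2.4.9), and nothing tells them to keep it from the assistant.

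**3. Do assistants record the outcome?** They do so only in teams without medical personnel. Section 2.4.4 contrasts first-division teams, which have such staff, with second-division coaches, who lack support and give first aid themselves. Assistant recording is therefore probably common in the trial, but no count is given. Where team medical staff record, section 2.4.4.5 claims no blinding for them, and they work inside an unblinded team.

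**4. Is there a later safeguard?** No section in the available text provides for injuries to be classified by someone without access to allocation. That text stops within Appendix B, so Appendices D, J and N could not be read.

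**5. How large could the bias be?** This is an illustration on assumptions. Let *s* be the share of injuries that are minor complaints open to discretion, and *d* the fraction of these missed in one arm only. With no true effect:

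- missed in the 11+ arm: rate ratio = 1 − *s·d*
- missed in the control arm: rate ratio = 1 / (1 − *s·d*)

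| *s* | *d* | Missed in 11+ arm | Missed in control arm |
|---|---|---|---|
| 0.3 | 0.1 | 0.97 | 1/0.97 = 1.03 |
| 0.5 | 0.1 | 0.95 | 1/0.95 = 1.05 |
| 0.5 | 0.3 | 0.85 | 1/0.85 = 1.18 |
| 0.7 | 0.3 | 0.79 | 1/0.79 = 1.27 |

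**6. What is the planned effect for comparison?** Section 2.4.4.3 assumes 70% injured, a 20% reduction, 90% power and 5% alpha, and states 125 per group. Reading the 20% as absolute (70% against 50%), the two-sided pooled formula without continuity correction gives [1.960·√(2·0.6·0.4) + 1.282·√(0.7·0.3 + 0.5·0.5)]² / 0.2² = 124, close to 125. Reading it as relative (70% against 56%) gives 248. The planned effect is therefore a ratio of 50/70 = 0.71. Missing 1 − 50/70 = 28.6% of injured players in the 11+ arm would mimic it.

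**7. Could smaller gaps matter?** Assume 70% truly injured in both arms, 125 per arm, and no allowance for clustering. If 5%, 10%, 15% or 20% of injured players in the 11+ arm go unrecorded, the chance of a significant result favouring the 11+ is about 9%, 21%, 41% or 63%. This covers one direction only; gaps in the control arm would work against the programme.

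**The case against.** The strongest reply is that section 2.4.4.5 describes a sensible practice, withholding allocation from assistants, and that no section says outright that they learn it. Definitions are printed on the back of the injury form (2.3.5.4), and assistants receive standardised training (2.3.6.1). Both limit discretion.

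Much of this stands, and it rules out several stronger readings that a reader might infer:

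- **Assistants are stationed with a team and watch its warm-ups.** The text says assigned. The regular contact it describes is fortnightly form collection, and practice visits belong to the researcher (2.4.6, 2.4.7.1).
- **Assistants record every injury.** They do so only where medical personnel are absent.
- **Assistants collect the 11+ forms each fortnight.** Section 2.3.6.1 limits that round to injury and exposure forms. The link to the 11+ forms runs only through the term research team.
- **Outcome assessment is known to be unblinded.** The documents support only that blinding is declared, not protected, and likely to fail.
- **The bias would favour the 11+ and match the planned effect.** The direction is unknown, since coaches trained to attend to injury might report more. The lowest illustrated ratio, 0.79, also falls short of the planned 0.71, and it compares a rate with a proportion.

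These limits narrow the point but do not remove it. Printed definitions do not settle whether a minor complaint gets reported, and an unprotected safeguard should not be presented as blinding.

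**Conclusion.** The point holds as a conflict within the plan: wrong as written, with a cheap improvement. Section 2.4.4.5 declares a blinding that sections 2.3.5.4, 2.3.6.1, 2.4.7.1 and 2.4.7.2 do not protect. Unblinding of assistants is likely, and the team medical staff who record elsewhere are not covered by the claim.

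The conclusion rests on two inferences: that research team carries the same meaning in section 2.4.7.2 as elsewhere, and that many second-division teams lack medical staff. The size and direction of any bias cannot be taken from the documents. The illustrated range of 0.79 to 1.27 depends wholly on the assumed *s* and *d*.

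**What to change.** 1. **Section 2.4.4.5.** Reconcile it with sections 2.3.5.4, 2.3.6.1, 2.4.7.1 and 2.4.7.2. Describe assistants as not informed of allocation, state who records injuries in each team, and do not claim blinded outcome assessment.
2. **Section 2.4.7.2, and 2.4.7.1 for the questionnaires.** Have the Appendix N forms and the post-training coach questionnaires collected and reviewed only by the researcher, who is already unblinded and visits practices.
3. **Supporting analysis.** Report the between-arm rate ratio with 95% CI, by the method of section 2.3.9, for injuries with at least 1 day of absence, beside the any-complaint result. If the main between-arm method changes, this analysis should follow it. The glossary's severity scale starts at 1 day, and the exposure form already records absence and its reason (2.3.5.3), so no new data are needed.

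**Cost.** Some rewording, slightly more form handling for the researcher, and one extra analysis with fewer events and a wider interval. The time-loss result depends less on whether minor complaints are written down. It is not free of bias, because unblinded coaches decide return to play (2.4.4). Sections 2.2 and 2.4.6 also place the first aid training in different arms and must be reconciled, since that training could affect absence too.

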### **2.4.5 Pre- and post-tests**

#### **2.4.5.1 Knowledge assessment questionnaire**

Questionnaires will be distributed to the coaches to assess their knowledge and belief related to injury prevention. Furthermore, coaches' readiness for injury prevention practice will be assessed prior to the intervention (Appendix K). The questionnaire will be comprised of 4

sections: section A will assess the demographic characteristics of the coaches including the age, highest coaching qualification, highest academic qualification, number of years coaching, number of years coaching first/ second division teams and number of years in the current team. In this section, they will also be asked whether they have received any first aid or injury prevention training. Section B assesses availability of the medical care in the team. Section C assesses injury prevention belief and practice readiness in key areas like planning injury prevention practice, use of protective equipment, checking playing field and facilities and up to date information. Section D assesses the first aid knowledge.

The validity and reliability of the questionnaire was established in a study conducted among high school coaches. The validity of the questionnaire was established during the two stage Delphi methods while the test-retest reliability was done to ascertain its reliability. Constructs pertaining to the stage of change, perceived susceptibility, benefits and self-efficacy were all Cronbach's alpha 70% and above (Siwon, 2013).

Looking at the fact that the knowledge constructs yielded a 39% Cronbach's alpha. An additional questionnaire used to assess the first aid and injury prevention knowledge was added to the previous one. The questions were developed by the American Red Cross after completion of first aid and sports injury courses to assess the gained knowledge. Participants were required to score minimum 80% to obtain certificates.

The questionnaires originally written in English will be translated in Kinyarwanda. Kinyarwanda is the national language which is spoken by all the Rwandan people. The questionnaire will be translated into Kinyarwanda by the researcher and the expert from the Rwanda Red Cross. The Kinyarwanda questionnaire will then be back-translated into English by a professional translator. It will then be piloted among five coaches in schools. The consensus meeting will be held to discuss the divergent areas in the two versions.

#### **2.4.6 Intervention**

Coaches of the teams in the second division in the intervention group will be invited to attend the training. The intervention is comprised of a five-day training divided into two parts. The first part of the training is the “11+” injury prevention programme while the second part is the training on first aid.

##### **The “11+” injury prevention programme**

The intervention programme “The 11+” will be introduced to coaches during the training (Appendix L). Coaches will be instructed on the 15 evidence-based exercises and the promotion of Fair Play. They will be instructed on how the exercises focus on core stability, balance, dynamic stabilization, and eccentric hamstring strength and their effects on frequent injury prevention. On field practical demonstration will also be conducted. At the end of the training, each coach will receive a DVD of the exercises and the total programme instructions and a booklet for reference. Coaches will be instructed to use the training programme at least 3 times a week and at every match and will record dates and times of using the training programme. Coaches will be visited at team practice by the researcher two times a week to see if proper implementation is occurring and additional instructions will be provided where necessary. The intervention will be conducted during the preseason period, October 2015.

##### **First aid training**

The intervention is comprised of 2-day training where they will be trained on first aid measures. Coaches will be trained on acute on-field, airway and concussion injuries management (Appendix M). A brief anatomy of some structures of the body (ankle, knee, shoulder, hamstrings, spine, and head) will be taught to the coaches ([www.boksmart.co.za](http://www.boksmart.co.za)). Quick on field assessment of the injured player and guidelines on when to remove a player from the field will also be provided using the SALTAPS and PRICE guidelines developed by F-MARC ([www.fifa.com](http://www.fifa.com)).

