Appendix H: INFORMATION SHEET FOR PLAYERS' PARENTS OR LEGAL GUARDIANS

Appendix I: INFORMED CONSENT FORM

Appendix J: DATA ANALYSIS TABLE

Appendix K: QUESTIONNAIRE FOR COACHES

Appendix L: 11+ WARM UP EXERCISES

Appendix M: CONTENT FOR THE TRAINING

Appendix N: THE "11+" RECORDING FORM

## GLOSSARY OF TERMS

**Coach:** One who instructs players in the fundamentals of a competitive sport and directs team strategy (Merriam-Webster Online Dictionary, 2010).

**Exposure factor:** Individual participation time recorded (Hägglund, Waldén, & Ekstrand, 2006)

**Recurrent injury:** injury of the same type and at the same site which occurs after a player's return to full participation within two months (Fuller et al., 2006).

**Injury prevention:** the implementation of interventions to eliminate or reduce the likelihood and the severity of injuries caused by external or internal mechanisms before they occur (Lawrence, 2008).

**Injury severity:** Based on absence from game or practice participation: slight (1–3 days), minor (4–7 days), moderate (8–28 days), major (>28 days) (Fuller et al., 2006).

**Rehabilitation:** A player is considered injured until given clearance by medical staff to participate fully in team training and match play (Hägglund et al., 2006).

**Soccer Injury:** Any physical complaint resulted for soccer participation whether in training or match (Junge & Dvorac, 2000).

**Training session:** Coach directed physical activities (on field, gym, recovery sessions, aerobics) carried out with the team (Hägglund et al., 2006).

**Readiness for injury prevention:** Coach related factor that is assumed to influence sports injury outcomes (Siwon, 2013).

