introduced to the coaches. Additional training will be provided to the coaches of the teams in the control group pertaining to first aid and injury treatment, rehabilitation. It is believed that this study will take into consideration the knowledge and uptake of the introduced injury prevention measures. At the end of this study, injury prevention context will be identified that will help to propose a well tailored countrywide intervention as described in the stage five and six of the TRIPP framework.

Table 1: The TRIPP framework for research leading to real-world sports injury prevention

| STAGE | MODEL                                                            | Scope of the study                                                               |
|--------------|-------------------------------------------------------------------------|-----------------------------------------------------------------------------------------|
| 1            | Injury surveillance                                                     | Study 1
Injury surveillance system                                            |
| 2            | Establish etiology and mechanism of injury                              |                                                                                         |
| 3            | Develop preventive measures                                             | Study 2
Comprehensive primary, secondary and tertiary prevention intervention |
| 4            | Ideal condition / Scientific evaluation                                 |                                                                                         |
| 5            | Describe intervention context to inform implementation strategies       | Conclusions and recommendations                                                         |
| 6            | Evaluate effectiveness of preventive measures in implementation context | Dissemination                                                                           |

(Finch, 2006)

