#### **2.4.4 Participants**

Coaches and assistant coaches of the teams in the second division teams will participate in this study. The coaches have been the center of focus in recent years as the main actors in the development of soccer in Rwanda. Much training has been organized by FIFA and CAF to enhance the knowledge and practice of the coaches. Trainings pertaining to technical, tactical and physical performance of the players were provided. At the end of the training, coaches are provided certificates. Not all coaches in Rwanda are citizens and not all of them had the same training. There are therefore some differences that may arise from their coaching training, background and experience.

The coaches are required to plan and supervise training sessions to develop the fitness and the skills of the payers. Coaches are responsible for the development of the training sessions according to the demands of the competition and the period of the season. The involvement of the coach in the first division teams concerning injuries in Rwanda is relatively less compared to the coaches in the second division because the teams have medical personnel who provide assistance. They also have assistant coaches, sometimes goalkeeper coaches, and kit managers. Coaches in the second division do not have all the support needed for their work. Working with

young players, they are required to act as organizers, parents, teachers, counselors, discipliners, for them to achieve results. In the case of injuries, coaches are looked at as mature and responsible people to provide first aid, preliminary management and advice for treatment. Coaches are further responsible to allow the players to return to play after injuries.

There are 19 teams in the second division and each team has at least one head coach. The minimum number of coaches of the teams who will receive the training is 19. The assistant coaches and goalkeeper coaches of the teams in the intervention study will also participate in the study even though not all the teams have them. The total number of players participating in the in the second division league is 570.

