## **2.4.7 Procedure**

### **2.4.7.1 Data collection**

Ethical approval, permissions and consent would be obtained during season one before conducting the study. Translation of the questionnaires into Kinyarwanda will be done before the pilot study. The translated questionnaires will be piloted among licensed five soccer coaches at school level to assess for clarity and responsiveness. A meeting will be held with them to discuss any unclear question from the translated versions and possibilities for better refining them.

During the preseason period, questionnaires assessing the knowledge of coaches regarding injury prevention will be distributed to coaches and appointment will be made for collection of the filled questionnaire. Questionnaires will be collected either by the researcher or the research assistants. Information pertaining to the availability of the medical personnel will also be obtained from the questionnaires.

Because of the changes that might take place at the end of the first season, coaches will again be invited to answer the knowledge questionnaires that will be distributed to them during the preseason period. Any other changes that will take place will also be noticed before the start of the season 2015-2016 as to the arrival of the new or change of the coaches, new teams registering into the second division league or new medical personnel arriving into the teams.

During the preseason period, July-August 2015, all the head, assistants and goalkeeper coaches of the teams in the intervention group in the second division will be invited to the training. The first part of the training will be conducted in two days where they will be taught about injury prevention in general and more specifically the importance and the use of the “11+” warm up programme. The first day will be for introduction and theoretical explanation of the conduct of the “11+” exercises while the second day will be reserved for practical demonstrations. The training will be provided by the researcher. Coaches will also be introduced to the recording of the use of the exercises while in the teams. The recording will be emphasized to ensure compliance. At the end of the training, the coaches will be provided DVDs, pamphlets and the FIFA link (where they could download the materials for free) of the exercises and will be

requested to use the “11+” as the warm up programme at least three times a week and before each match that the team will play.

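### The sections disagree on which arm's coaches receive first aid training; if only one arm does, an any-complaint outcome risks differential ascertainment, and no less exposed between-arm result is planned

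*Combined protocol and SAP*

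**What the plan says.** **Who is trained.** Section 2.4.6 states: "Coaches of the teams in the second division in the intervention group will be invited to attend the training". It describes two components: "The first part of the training is the “11+” injury prevention programme while the second part is the training on first aid". Section 2.4.7.1 repeats the restriction, naming the head, assistant and "goalkeeper coaches of the teams in the intervention group in the second division will be invited to the training". Section 2.2 says something different: "Additional training will be provided to the coaches of the teams in the control group pertaining to first aid and injury treatment, rehabilitation". Section 2.4.4 puts the minimum number of coaches receiving the training at 19, which is the number of second-division teams. Section 2.4.9 says only that control teams keep their usual warm-up and does not mention first aid.

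**What is taught.** Under First aid training, coaches learn management of acute on-field, airway and concussion injuries. In addition: "Quick on field assessment of the injured player and guidelines on when to remove a player from the field will also be provided".

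**What is counted.** The Glossary defines a soccer injury as "Any physical complaint resulted for soccer participation whether in training or match". Section 2.3.5.4 adds that medical attention is not a criterion.

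**Who records it.** Section 2.3.5.4 gives the injury form to team medical personnel, or to a research assistant where a team has none. Section 2.4.4.5 assigns one assistant per team, intended to be blinded; coaches, players and the researcher are not blinded. Of second-division teams, 2.4.4 says "coaches are looked at as mature and responsible people to provide first aid, preliminary management and advice for treatment", and that coaches also allow return to play. The exposure form in 2.3.5.3, given to coaches, records absences and their reasons.

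**How the arms are compared.** Section 2.4.8 refers back to 2.3.9, which uses z-statistics and rate ratios with 95% confidence intervals.

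**The concern.** An outcome of any physical complaint has a very low threshold, so the count depends on what is noticed, mentioned and written down. Training that changes how coaches assess and remove injured players could alter what reaches the record, separately from any effect of the warm-up on how often players are hurt. If that training goes to one arm only, the rate ratio mixes the two.

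What is at stake depends on the arm. Extra recording in a trained intervention arm would pull a protective rate ratio towards 1 and hide benefit. Extra recording in a trained control arm would produce an apparent benefit with no true effect. The available text plans no between-arm rate comparison that is less sensitive to reporting.

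**Working it through.** **Step 1. Which arm is trained.** Three readings are open.

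| Reading | Support | Consequence for recording |
|---|---|---|
| Intervention only | 2.4.6 and 2.4.7.1 | possible excess in intervention arm |
| Control only (first aid) | 2.2, taken alone | possible excess in control arm |
| Both arms | 2.2 and 2.4.6 together; 19 coaches in 2.4.4 | differential largely disappears |

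**Step 2. The route into the record.** The coach does not complete the injury form. No section says how the medical person or assistant learns of each complaint. Section 2.3.6.1 says only that forms are collected every two weeks, by the researcher or the assistants. Because the coach deals with injuries first in these teams (2.4.4), the coach is a plausible informant. That is an inference, not something the plan states.

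**Step 3. Size under stated assumptions.** The documents give no recording probabilities, so these inputs are assumed:
- s, the share of complaints minor enough for recording to depend on recognition: 0.4 to 0.6. All other complaints are taken as always recorded.
- c0 and c1, the probability that such a complaint is recorded without and with coach training: 0.7 and 0.8 (mild), 0.6 and 0.8 (middle), 0.6 and 0.9 (strong).

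Recording ratio K = [(1 − s) + s·c1] / [(1 − s) + s·c0].

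- Smallest (s = 0.4, mild): (0.6 + 0.32)/(0.6 + 0.28) = 0.92/0.88 = 1.045
- Middle (s = 0.5): (0.5 + 0.40)/(0.5 + 0.30) = 0.90/0.80 = 1.125
- Largest (s = 0.6, strong): (0.4 + 0.54)/(0.4 + 0.36) = 0.94/0.76 = 1.237

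The observed rate ratio is the true one times K if only the intervention arm is trained, and the true one divided by K if only the control arm is trained.

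| K | True 0.80, intervention trained | True 1.00, control trained |
|---|---|---|
| 1.045 | 0.836 | 0.957 |
| 1.125 | 0.900 | 0.889 |
| 1.237 | 0.989 | 0.809 |

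A K of 1.25 would remove a true 0.80 entirely, since 0.80 × 1.25 = 1.00.

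**Step 4. The plan's own effect size.** Section 2.4.4.3 uses 70% injured, a 20% reduction, 90% power and alpha 5%, and states 125 per group. Reading the reduction as 20 percentage points (70% to 50%), two-sided, with pooled variance:

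n = [1.96·√(2 × 0.6 × 0.4) + 1.2816·√(0.7 × 0.3 + 0.5 × 0.5)]² / 0.2² = (1.358 + 0.869)² / 0.04 = 124.

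This agrees with 125. The implied ratio is 0.50/0.70 = 0.714. If extra recording multiplied the intervention proportion by K, power at 125 per group would be:

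| K | Recorded proportion | Power |
|---|---|---|
| 1.00 | 0.500 | 90% |
| 1.05 | 0.525 | 81% |
| 1.10 | 0.550 | 69% |
| 1.20 | 0.600 | 38% |

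These powers ignore clustering and apply K to the proportion of players injured, so they show sensitivity only; they are not the trial's power.

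**The case against.** The strongest reply is that the plan separates recording from coaching. Medical personnel or an assistant complete the form, and the assistant is meant to be blinded. This stands and weakens the mechanism. It does not remove it, because blinding the recorder does not help if the information reaching the recorder already differs between arms, and the plan is silent on that step. The two-weekly collection of forms is no evidence either way: it does not show who informs the recorder.

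Second, the training described concerns acute management and assessment of a player already seen to be injured. A complaint starts with the player, so a large gain in recording of minor complaints is not obvious. This also stands, and it is one reason to treat the upper figures as the end of an assumed range. Appendix M, which holds the training content, is not in the available text.

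Third, removal guidance may genuinely prevent aggravation or re-injury. Table 1 describes study two as primary, secondary and tertiary prevention, so some change in counts could be real effect.

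Fourth, severity is already graded and tested by chi-square (2.3.9). That tests a distribution of injuries and is not stated to be a between-arm rate. Appendix J, also unavailable, may say more.

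A reader might infer that exactly one arm is trained whichever section is followed, or that the training is bound to change the count and bias the rate ratio in a known direction. The documents support neither. Sections 2.2, 2.4.4 and 2.4.6 together allow training in both arms, and nothing in the plan quantifies recording.

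**Conclusion.** The plan contradicts itself on which coaches receive first aid training. If one arm alone receives it, there is a risk of differential ascertainment whose size is unknown and whose direction depends on how the contradiction is resolved. The assumed K of 1.05 to 1.24 moves a true 0.80 to between 0.84 and 0.99 (intervention trained), or a true 1.00 to between 0.96 and 0.81 (control trained). These ranges rest wholly on the assumed s, c0 and c1. They show that a modest recording difference would be of the same order as the effect sought; they do not show that such a difference will occur. This is a worthwhile, inexpensive improvement and not a demonstrated bias.

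**What to change.** 1. Reconcile 2.2, 2.4.4, 2.4.6 and 2.4.7.1 on which arm's coaches receive first aid training. This costs only text.

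2. In 2.4.8, pre-specify the between-arm rate ratio with 95% CI for injuries with more than 7 days' absence (the Glossary's moderate and major grades, already recorded), beside the all-complaint rate ratio. State that a difference confined to slight or minor complaints, or to those with no absence, may reflect recognition or reporting and will be interpreted with caution. This is one more analysis of data already collected. Its price is fewer events and a wider interval. Because coaches influence removal and return, absence can itself shift, so this result is less exposed than the all-complaint one but not immune.

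3. In 2.3.5.4, say how the person completing the injury form learns of complaints. If a scripted enquiry to players by the assigned assistants is used, it should be identical in both arms and in both seasons. Section 2.4.7.1 keeps season-two collection the same as season one, and objective a in 2.4.2.1 compares injuries before and after the programme. Adding active questioning in season two alone would disturb that comparison. The main change in item 2 does not depend on it.
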